#### Inclusion Criteria

Participants will be included according to the following inclusion criteria: (1) age from 50-75 years, (2) BMI from 18.5 to 32.49 kg/m², (3) ability to walk without walking aids at baseline assessment, (4) scheduled for elective unilateral THA, (5) willingness to comply with all study-related procedures, and (6) providing informed consent.

#### Exclusion Criteria

Participants will be excluded in the case of (1) symptoms of delayed healing concerning the implant, (2) cardiorespiratory symptoms limiting exercise therapy (eg, severe heart disease), (3) symptoms of musculoskeletal or cardiorespiratory overload, (4) neuromotor diseases (eg, previous stroke, multiple sclerosis, Morbus Parkinson disease), (5) other reasons that would lead to obvious limitations concerning participation in the intervention (eg, severe contralateral OA, lower extremity fractures within the past 12 months, other elective lower extremity surgery within 6 months, inadequacy in German concerning questionnaires and exercise instructions, mentally unable to participate), and (6) nonadherence (see the definition in the *Therapeutic Adherence* section).

#### Recruitment

Patients scheduled for elective unilateral THA at the Orthopedic Hospital Speising will be informed by their orthopedic surgeon of an opportunity to participate in the study. If interested, they will be checked for eligibility by physicians. One of the enrolling physicians is also acting as the principal investigator according to Austrian medicinal product law. In the case of willingness and eligibility of the potential participant, written informed consent will be obtained by the informing and enrolling physician from the participant prior to surgery. On the day of discharge, participants will be finally checked by a physician concerning their status of recovery with regard to the exclusion criteria.

Clusters for the intervention phase have been defined as groups of 2-5 patients starting their collective training program at the same time. Due to logistics, only 1 clustered group will be considered at a time. The group exercise program will be the same for both the IG and the CG and will only differ in the home exercise program, which for the IG will be supported by a digital real-time exercise feedback prototype for digitally guided training. Patients who belong to the same cluster will be randomized to receive the same treatment. Clusters after baseline assessment will be randomized in blocks (block size blinded) by means of an online random sequence generator [27] to achieve equal allocation of clusters to both arms. Due to the small number of clusters (about 20), no stratified randomization approach will be applied. Patients will be arbitrarily clustered based on the surgery date. Due to the nature of the studied conditions, it will not be possible to blind researchers.

Patients’ active participation will take 6 hours for assessments performed at baseline, 3-month, and 6-month follow-up. They will be offered a maximum of possible supervised exercise sessions of 24 hours and will be required to practice their home exercise program for 20 hours over the intervention period of 8 weeks. Shopping vouchers of €220 (US $239) will be offered as an incentive for participation.

#### Safety Considerations

Adverse events are unlikely. Participants will be clinically assessed prior to the baseline measurement and the intervention. Exercise therapy will be guided and supervised by a physiotherapist. Information about patients’ settings at home regarding exercising space, safety, and possible risks will be retrieved, and if necessary, on-site visits to ensure safe home exercising will be performed. All participants will be insured through clinical trial insurance.

Medical and technical quality of the baseline assessment, intervention, and follow-up assessment will be guaranteed through written documentation of monitoring visits by the principal investigator and the designated clinical investigation monitor. This documented supervision will be carried out for the first 2 patients and the first group exercise session.

### Examination Procedures

In the examination, initial status interviews including questions on personal data, such as age, gender, and insurance, and on health in terms of a health check will be conducted at t_0_ (baseline 4-6 weeks postsurgery), t_1_ (3 months postsurgery), and t_2_ (6 months postsurgery). In particular, current pain in the surgical area, its occurrence and severity, and previous injuries and any other general medical interventions or complaints in the leg, pelvis, and spine during the past 6 months will be reviewed. Finally, participants will be asked about medications and known systemic diseases. The status interviews at t_1_ will also incorporate questions on usability of the feedback prototype (IG) and on exercise adherence and subjective feelings concerning exercise execution, while status interviews at t_2_ will include questions on exercise behavior and whether patients can incorporate exercising into their daily routine. All details concerning status interviews can be found in Multimedia Appendix 1. Within the status interviews, patient reported outcome measures (PROMs) will be gathered. The individual pain level on the 10-item Numeric Rating Scale (NRS-10), with focus on the surgery region, will be noted. In addition, the standardized PROM HHS (prior to surgery, t_0_, t_1_, and t_2_) and the HOOS [28], SF-12 [29,30], and the IPAQ-SF [31] at t_0_, t_1_, and t_2_ will be explained to the participants, and they will be asked to fill them out as part of the status interviews. If a participant reports additional problems with the knee joint, they will be asked to fill out the KOOS [32] at t_0_, t_1_, and t_2_. At t_1_, participants in the IG will also be asked to fill in their system usability score (SUS) for quantitative assessment of the usability of the real-time exercise feedback prototype.

**Table 2 table2:** Tasks performed during assessments and estimated duration in minutes.

Task	Repetitions/valid strikes	Estimated duration (minutes)
Interview status	1	10
Questionnaires	1	15
Height/body composition	1	5
Instruction activity monitor	1	5
RoM^a^/muscles	1	10
Applying markers/distances	1	10
Calibration	1	7
LW^b^ right/left	5	8
STS^c^/STSr^d^	5	5
TuG^e^	3	5
SQL^f^	5	5
UP^g^/DOWN^h^ right/left	5	20
SUP^i^/SDOWN^j^	5	7
Demounting markers/check	1	8

^a^RoM: range of motion.

^b^LW: level walking.

^c^STS: sit to stand.

^d^STSs: sit to stand reverse.

^e^TuG: timed up and go.

^f^SQL: squat lifting.

^g^UP: ramp-up walking.

^h^DOWN: ramp-down walking.

^i^SUP: stair-up climbing.

^j^SDOWN: stair-down climbing.

#### Level Walking

Participants will be instructed to walk self-paced at a comfortable speed between start and end marks. Familiarization trials will be carried out in the preparatory phase.

#### Timed-Up-and-Go Test

Participants will be instructed to start on a “go” signal with rising from a chair, walking 3 m, turning beyond the 3 m line, returning to the chair, and sitting down again. Considering the performance learning effect in performing the test, 2 familiarization trials will be carried out in the preparatory phase.

#### Sit-to-Stand and Sit-to-Stand-Reverse Tests

Participants will be instructed to stand up from a lower leg–normalized chair with self-paced speed, keep standing still, and, on the instructor’s signal, sit down again. Considering the performance learning effect in relation to the shank length–normalized seat height, 3 familiarization trials will be carried out in the preparatory phase.

#### Squat Lifting

Participants will be instructed to lift a box with a 5 kg weight inside with both arms and keep standing still for a moment. Considering the performance learning effect in relation to the height of the box, 3 familiarization trials will be carried out in the preparatory phase.

#### Ramp Walking

Participants will be instructed to walk up and down the ramp at a self-selected comfortable speed between start and end marks without using the handrail. Familiarization trials will be carried out in the preparatory phase with a 10° inclination.

#### Stair Climbing

Participants will be instructed to walk up and down the stairs at a self-selected comfortable speed with the whole foot placed on the single arrays without using the handrail. Familiarization trials will be carried out in the preparatory phase.

The examination procedure described before will be performed at baseline (t_0_) prior to the randomization and at 3 months (t_1_) and 6 months (t_2_) postsurgery. Follow-up assessments (t_1_ and t_2_) will be accompanied by a structured interview on exercise behavior and well-being. In addition, the IG will be interviewed concerning the acceptance of the RTF device and possible suggestions for improvements.

### Agreement Between the Real-Time Feedback System

The RTF prototype that will be provided to the IG for home exercise is a combination (Figure 2) of the Intel® RealSense Depth Camera D435i (Intel Corporation), the mini-PC Radxa Rock 5 Model B 8GB (Radxa Ltd), and a Raspberry Pi USB-C Power Supply. Using the Intel RealSense SDK 2.0, the red-green-blue (RGB) data are streamed to the mini personal computer (PC) for extraction of a 17-point kinematic model by the machine learning tool for pose estimation, MoveNet.SinglePose V4 (Google Inc). Via a self-programmed user interface operated using an infrared remote controller, the prior developed feedback modes can be selected and started.

**Figure 2 figure2:**
[figure not shown]
System components of the prototype.

The recorded image data, which may potentially identify a person, will be solely used for key point recognition purposes and will not be stored in any form. The RTF prototype has no wireless local area network (LAN), and the existing LAN connection is covered by the housing. Therefore, an internet connection is excluded and access from outside is not possible. The complete data processing will be carried out locally on the prototype. The following data will be stored on the SD card of the prototype: test person ID, body height, training time, achieved exercise scores, number of repetitions of the exercises, and coordinates of the key points. The SD card is located inside the housing, making it difficult to access or remove. The data from the SD card will be analyzed only by the project team and will not be passed on to third parties.

The prototype is not certified as a medical device and was therefore submitted to the Austrian Federal Office for Safety in Health Care for a safety review after a successful ethics vote. Relevant individual parts have a Conformité Européene (CE) mark of conformity.

To compare the RTF prototype with the optoelectronic reference system Vicon Nexus, both systems will be synchronized both temporally and spatially. Temporal synchronization will be achieved through a time-to-live (TTL) signal sent from the prototype to the reference system. Spatial synchronization will be ensured by calibrating the prototype’s coordinate system to match the reference coordinate system. For assessing this agreement, testing participants from the IG will perform a single set of their home exercise program at t1 after performing the set of ADL tasks.

### Group Exercise Program

Group exercise therapy will be guided by experienced physiotherapists in groups (as defined per cluster) of 2-5 patients. Patients will participate in 2 group exercise therapy sessions of 90 minutes each per week, with at least 48 hours of rest in between sessions during 8 consecutive weeks. Both the IG and the CG will be instructed and supervised in an equal program, which will only be individualized regarding intensity and repetitions, depending on each patient’s capacity. Group exercise therapy will take place in a suitable room at FH Campus Wien, which will be equipped with the necessary therapeutical/exercise therapy equipment and supplementary aids. At the beginning of each session, the well-being of participants will be assessed and documented.

To ensure self-paced intensity and number of repetitions for participants during the group exercise therapy sessions, time-based sets of 60 seconds will be used. Within those sets, fixed breaks of 60 seconds for recovery will be implemented. For each exercise used in the protocol, variants with decreased and increased intensity will be offered to the participants to ensure appropriate stimulus. Both group exercise therapy interventions and the home exercise program for the IG and the CG will follow the frequency, intensity, time, and type of training (FITT) principle for exercise prescription and will be reported following the Consensus on Exercise Reporting Template (CERT) [34]. The group exercise therapy intervention will consist of a 15-mintue warm-up, 60-minute exercise, and a 15-minute cool-down phase. During the group -exercise phase, patients will be instructed to complete exercises, with focus on movement quality, and if applicable, for specific exercises, they will be instructed to perform the concentric phase of each repetition fast, shortly maintain the individual end-of-range tension, and slowly perform the eccentric phase to reach an approximate time under tension of 5-6 seconds per repetition. The physiotherapists will provide verbal guidance, encouragement, and motivation during the group exercise therapy intervention. With this self-paced protocol, participants will reach approximately 8-12 repetitions per set. The intensity of each exercise will be increased or decreased following participants’ self-reported perceived rate of exertion with the help of the Borg CR10 scale [35]. Intensity will be increased if participants rate an exercise below 4 and decreased if they rate an exercise higher than 7. For all participants, the absolute exercise therapy load will be recorded. Patient-reported hip pain before and after exercise sessions will be assessed during warm-up and cool-down using the NRS-10, graded from 0 (no pain) to 10 (worst pain imaginable). Pain levels from 0 to 2 will be considered safe, from 3 to 5 acceptable, and >5 as not acceptable. On the following day after the exercise therapy intervention, pain should be reduced to the participants’ usual level, or the load will be decreased in the next session. Table 3 presents an overview of the intervention, and a detailed list concerning the planned exercise therapy intervention program, including exercise variants and steps of progression, can be found in Multimedia Appendix 2 following the CERT checklist [34].

**Table 3 table3:** Structure and content of exercise sessions.

Phase	Description	Duration (minutes)
Warm-up	Each session will begin with a warm-up for general activation, starting with assessing the individual well-being/pain level of participants and continuing with simple and self-paced exercises in the sitting and standing positions.	15
Exercise	Sitting exercises: forefoot eversion with loop, activation exercises for lower limbs. Floor exercises in supine and side positions + exercise mat): bridging, clam-shell, abduction/adduction exercises. Standing exercises: pelvic hinge, squat, mini-SLS^a^, flexion/extension/abduction/adduction exercises. Gait training: gait phases, step up, lunge, calf raise.	60
Cool-down	Each session will end with a 15-minute cool-down for reflexion, starting with simple and self-paced stretching/mobilization in sitting and standing positions, assessing the individual well-being/pain level of participants postexercise, and reporting the total exercise load of the session.	15

^a^SLS: single-leg stance.

### Home Exercise Program

In addition to semiweekly exercise therapy sessions, a daily 30-minute home exercise program, excluding days with the group exercise program, will be performed by participants. The home exercise program will be self-documented by the participants in an exercise diary, including the day, the exercises performed, number of repetitions, pain on the NRS-10, and perceived exertion on the Borg CR10 scale [35].

Both groups will receive printed handouts describing each exercise, as well as the full home exercise program in detail. Both groups will also receive standard care treatment, including the same group exercise and home exercise programs. The IG group will perform the home exercise program supported by the digital real-time exercise feedback prototype for digitally guided training (Figure 3).

**Figure 3 figure3:**
[figure not shown]
Example of the feedback presented for a single exercise.

#### Therapeutic Adherence

Adherence to the therapeutic control and intervention will be recorded based on (1) participation in 16 group exercise sessions and (2) self-reported adherence to 40 home exercise sessions. Participants will be classified as nonadherent (and consequently excluded from the analysis) if participation is below 25% of the group exercise sessions (ie, less than 4 sessions) or below 25% of the home exercise sessions (ie, less than 10 sessions). Based on further 50% and 75% cutoffs, therapeutic adherence will be classified into (1) nonadherent, low, medium, or high.

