**Assessments**															
	3D movement analysis	—		—		✓		—		—		✓		✓	
	Clinical status	—		—		✓		—		—		✓		✓	
	Body composition analysis	—		—		✓		—		—		✓		✓	
	7-day activity monitoring	—		—		✓		—		—		✓		✓	
	PROMs^k^	—		—		✓		—		—		✓		✓	

^a^Enrollment will be 4-10 days prior surgery.

^b^Baseline t_0_ is 4-6 weeks postsurgery.

^c^Randomized allocation will be conducted at the end of baseline assessment.

^d^8 weeks.

^e^3 months postsurgery.

^f^6 months postsurgery.

^g^Not applicable.

^h^HHS: Harris Hip Score.

^i^RTF: real-time feedback.

^j^CG: control group.

^k^PROM: patient-reported outcomes measure.

The number of participants assessed for eligibility, allocated to study arms, and analyzed will be recorded using the CONSORT (Consolidated Standards of Reporting Trials) extension flowchart on cluster randomized trials [23]. Figure 1 illustrates the trial design and participant flow through the trial. The protocol is according to SPIRIT (Standard Protocol Items: Recommendations for Interventional Trials) reporting guidelines [24].

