### Statistical Analysis

Data will be inspected for outliers using boxplots. Shapiro-Wilk tests and additional graphical inspections of q-q plots will be applied to test for the normality assumption. Metric baseline characteristics will be indicated as means (SDs) and categorical baseline characteristics as frequencies (n, %). Unadjusted outcome scores will be reported as means (95% CIs). People from the same cluster tend to be more similar than those from different clusters, and the analysis must allow for this. A common enhancement is to apply a linear mixed effects model with the cluster specified as a random intercept. To model changes between baseline and follow-up, we will include baseline measurements as covariates. Following suggestions by Klar and Darlington [37], we will adjust for each participant’s baseline assessment and for the baseline cluster mean. Otherwise, no adjustments for covariates are foreseen. Treatment effects will be reported independently for follow-up t_1_ and follow-up t_2_, including unstandardized and standardized regression coefficients as effect estimates, standard errors, *t* statistics, and appropriate *P* values via the Satterthwaite degrees-of-freedom method. Between-cluster and residual variances will be reported for all outcomes. In the case of severe outliers or major violations of the normality assumption, logarithmic data transformation approaches will be explored. Outcome parameters on the ordinal scale will be analyzed descriptively and reported as medians with ranges. All descriptive statistics and corresponding numbers of subjects (n, %) will be reported, along with losses to follow-ups. Effect sizes will be calculated and reported accordingly (per protocol). In addition, the hypotheses will be analyzed according to the intention-to-treat principle (last value carried forward), providing a more conservative effect estimate [38] when missing observations introduce bias. The α value will be set to .05, and exact 2-sided *P* values will be reported. Hypotheses will be tested independently of each other. The 2-armed study design does not require post hoc tests, so no adjustment for familywise α error accumulation is needed.

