## Discussion

### Principal Findings

RTF-supported home exercise is expected to improve exercise execution quality and therapeutic adherence compared to using paper instructions for exercise guidance. As a consequence thereof, we anticipate superior results for the selected outcome measures in the IG.

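### Patients are dropped for nonadherence after randomisation and the per-protocol analysis leads, although the feedback device is expected to change adherence, so the main comparison loses the protection of randomisation

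*Protocol article*

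**What the plan says.** Footnote c to Table 1 fixes the timing: "Randomized allocation will be conducted at the end of baseline assessment". The 8-week programme follows, and adherence is counted over 16 group sessions and by "self-reported adherence to 40 home exercise sessions".

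The Therapeutic Adherence section then sets the rule: "Participants will be classified as nonadherent (and consequently excluded from the analysis) if participation is below 25% of the group exercise sessions" (fewer than 4 of 16), or "below 25% of the home exercise sessions (ie, less than 10 sessions". The Exclusion Criteria repeat it as their last item, "and (6) nonadherence", with a cross-reference to that definition.

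The Statistical Analysis section says: "Effect sizes will be calculated and reported accordingly (per protocol". It then adds an analysis by intention to treat, with the last value carried forward.

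Under Principal Findings the authors write: "RTF-supported home exercise is expected to improve exercise execution quality and therapeutic adherence". They expect better outcomes in the intervention group (IG) as a result.

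**The concern.** Eligibility is checked before surgery and again at discharge. Nonadherence cannot be known at either point, so as an exclusion criterion it can only remove patients who have already been randomised.

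By the protocol's own reasoning, adherence lies on the path from RTF to outcome. Restricting the comparison to adherers has two consequences. First, if RTF works partly by keeping patients exercising, removing the control group (CG) patients who stopped hides that part of the effect. Second, the patients removed from each arm may differ in kind. Some may stop because of pain and others because they feel well, so the bias could go either way.

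The home criterion adds a further route. It rests on self-report by patients who know which programme they have. The prototype stores training time and repetitions, so self-report can be checked against a device record in the IG but not in the CG.

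All three primary outcomes are affected, at both follow-ups.

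**Working it through.** **1. The plan's own figure.** Inputs from the Sample Size section: d = 0.8, 24 per group, clusters of 3, intracluster correlation 0.05, α = .05 (two-sided, per the Statistical Analysis section).
- Design effect: 1 + (3 − 1) × 0.05 = 1.10.
- Effective n per arm: 24 / 1.10 = 21.8.
- Power: Φ(0.8 × √(21.8/2) − 1.96) = Φ(0.68) = 0.75.

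The stated power of 0.75 reproduces, so this point does not rest on a sample-size error.

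**2. Size of the selection bias.** The protocol gives neither nonadherence rates nor a correlation between adherence and outcome; both are assumed here. Model: no true treatment effect; latent adherence is standard normal and correlates r with an outcome scored so that higher is better (SD 1); the least adherent fraction p is excluded in each arm.

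Mean shift among those kept: r × λ(p), where λ(p) = φ(z_p) / (1 − p).

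Bias (IG minus CG): r × [λ(p_IG) − λ(p_CG)].

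For p = 0.05, λ = 0.109; for p = 0.20, λ = 0.350.

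| Excluded IG / CG | r = 0.3 | r = 0.5 |
|---|---|---|
| 5% / 5% | 0 | 0 |
| 5% / 15% | −0.05 | −0.08 |
| 5% / 20% | −0.07 | −0.12 |
| 10% / 30% | −0.09 | −0.15 |
| 5% / 30% | −0.12 | −0.19 |

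Worked case: 0.5 × (0.109 − 0.350) = −0.121 SD; with r = 0.3, −0.072 SD.

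The 5%/20% and 10%/30% rows span 0.072/0.8 = 9% to 0.151/0.8 = 19% of the planned effect. Reversing the sign of r (nonadherers recover better) gives the same sizes in favour of RTF.

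**3. Effect on the test.** Starting from 35 per arm with design effect 1.10, the two-sided type I error is about 0.06 to 0.08 for the 5%/20% and 10%/30% rows at r = 0.3 to 0.5. It is about 0.07 to 0.11 for 5%/30%, against a nominal 0.05.

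**4. What an as-randomised analysis would cost in power.** Assume that outcomes are obtained for all 70 (35 per arm, effective n 35/1.10 = 31.8) and that nonadherers gain nothing from RTF, so d = 0.8 × (1 − share nonadherent).

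| Nonadherent | d | Power |
|---|---|---|
| 0% | 0.80 | 0.89 |
| 5% | 0.76 | 0.86 |
| 10% | 0.72 | 0.82 |
| 20% | 0.64 | 0.72 |
| 30% | 0.56 | 0.61 |

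**The case against.** The strongest reply is that a randomised comparison is already planned: the same hypotheses are to be analysed by intention to treat, and the article never labels either analysis primary. This stands in part. That per protocol leads is read from the order and from intention to treat being introduced as an addition. However, no reading puts intention to treat first. The adherence rule also removes patients from the analysis without limiting this to a per-protocol set. Taken literally together with the exclusion criterion, it could remove them from the intention-to-treat set as well.

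Second, differential exclusion is expected rather than shown. The 25% bar is low, and the group programme is the same in both arms, so RTF would act mainly through the home criterion. This is fair: if few patients fall below the bar, or equal and similar fractions do in each arm, the bias is small or nil.

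Third, the illustrated bias is modest beside sampling error. With 24 per arm the standard error of d is about √(2 × 1.10/24) = 0.30, so 0.07 to 0.15 SD is roughly a quarter to a half of one standard error, and in the modelled direction it would not produce a false claim for RTF. But the direction is unknown beforehand, and a reader could not correct for it afterwards. Pilot status does not remove the problem either, because two-sided tests at .05 are planned.

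Fourth, carrying the last value forward weakens the planned intention-to-treat analysis. For a patient with no follow-up it uses the value from 4-6 weeks after surgery, so it is not assured to be conservative. That is a separate matter, and it does not justify leading with per protocol.

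**Conclusion.** The concern holds. The rule excludes randomised patients for behaviour that arises after allocation and that the protocol expects the intervention to change, and the analysis using this rule is reported first. This follows from the text and needs no assumption about rates.

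The size does depend on assumptions. Under sharply unequal exclusion (5% versus 20%, or 10% versus 30%) and a correlation of 0.3 to 0.5, the bias is 0.07 to 0.15 SD, in a direction that cannot be known in advance. It could be close to zero if few patients are excluded. The rule should be corrected before any outcome comparison is run, because it touches every primary comparison and follow-up data not collected from nonadherers cannot be recovered.

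**What to change.** - Delete nonadherence, item (6), from the exclusion criteria.
- State that the primary analysis includes all randomised participants, in the arm to which their cluster was allocated, whatever their adherence.
- Keep the per-protocol set (at least 25% of group and of home sessions) and the adherence categories as a labelled sensitivity or descriptive analysis.
- State that t1 and t2 assessments continue for nonadherent participants.
- Reconcile the Exclusion Criteria, Therapeutic Adherence and Statistical Analysis sections so that each names the set it refers to.

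The cost is mainly wording, since the t1 and t2 visits are already scheduled. Because version 3.3 has ethics approval and the trial has started, a formal amendment may be needed. The statistical price is some dilution of the estimate by nonadherers: slight if they are few, larger if they approach 20% to 30%.
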